### Moringa Leaf Extract Supplementation

#### Collecting Moringa Leaves

The moringa leaves used in this study were collected from moringa trees growing in the Gowa and Takalar regencies. Fresh and healthy leaves were used for supplementation. The leaves chosen were mature, dark green leaves from the tenth stalk down from the tip of the branches. A previous study [33] has shown that mature moringa leaves exhibit a higher antioxidant activity than younger leaves.

#### Washing and Drying

The harvested moringa leaves were washed by dipping them in water and rinsing them several times with running water to remove any dirt or impurities. After washing, the leaves were air-dried for 2 h to remove the excess water. The leaves were separated from the stalks. The drying process was conducted out in an oven at a temperature of 30‐40 °C for 3‐4 hours or until the leaves reached a moisture content of less than 10%.

#### Extraction

The dried moringa leaves were ground into a fine powder using mesh 60. The powder was extracted using distilled water (Aquadest). The extraction process involved soaking moringa powder in distilled water, after which the mixture was squeezed and filtered through a muslin cloth to separate the extract from the residue. The obtained extract was further processed using a rotary evaporator and dried using a freeze dryer until a dry extract was produced.

#### Capsule Supplement Production

The dry extract was ground again using mesh 100 to obtain a fine extract powder. This powder was then mixed with corn starch as a filler in a 4:1 ratio (400 mg of moringa extract and 100 mg of corn starch per capsule). Each capsule contained 400 mg of moringa leaf extract. Participants in the intervention group received 2 capsules twice daily (totaling 2000 mg/d) for a period of 8 weeks, beginning immediately upon enrollment (between gestational weeks 20‐32). In cases where participants gave birth before completing the 2-month supplementation period, they were instructed to continue consuming the remaining *M. oleifera* supplements until the full course was completed. This approach aimed to ensure consistency in the intervention dosage, regardless of the timing of delivery, and to maintain the study’s internal validity.

#### Quality Control

After production, supplementation with moringa leaf extract capsules was tested to ensure weight uniformity and quality, including checks for moisture content, microbial presence, and organoleptic tests to ensure product safety and quality. The dosage of moringa leaf supplementation in this study was determined based on several previous safety studies [34-36], which indicated that the consumption of moringa leaves is safe at doses up to 2000 mg/day for humans and has the potential to be a safe source of antioxidants for pregnant women.

### Participant Recruitment

This research has been conducted in Makassar City, specifically at 6 community health centers where expectant women receive prenatal services. The 6 selected community health centers are located in areas with varying environmental characteristics, including industrial zones, regions near landfill sites, and coastal areas. While the types of pollution sources differ, all sites share a common feature: exposure to potential environmental contaminants. Each represents an urban setting with a plausible risk of heavy metal exposure through air, water, and food pathways. Thus, despite differences in specific pollution types, the study sites are considered comparable in terms of overall environmental risk exposure. This selection strategy ensures that the intervention and control groups are drawn from communities facing similar environmental health challenges. Moreover, such variation may enhance the generalizability of findings across different urban pollution contexts. Three centers were assigned as intervention sites and 3 as control sites based on operational convenience and to avoid information spillover between groups.

The study will include 59 pregnant women in each group of intervention and control who underwent an examination at health centers in Makassar and fulfilled the following inclusion criteria: (1) pregnancy during the second or third trimester, (2) intention to deliver in Makassar, (3) living in Makassar for a period exceeding 1 year, and (4) blood levels of Hg, Pb, or Cd exceeding the reference value. Participants will be excluded based on self-report during interview if they (1) are having twin pregnancy, (2) had known chronic medical conditions, such as diabetes, cancer, kidney diseases, (3) are taking other antioxidant or mineral supplements beyond standard care, (4) are diagnosed with micronutrient deficiencies, (5) relocate during the intervention period, and (6) are unwilling to comply with follow-up procedures.

The required sample size was calculated using an estimated effect size (Cohen *d*) of 0.42, derived from a previous intervention study in South Sulawesi, which assessed the effects of *M. oleifera* supplementation on oxidative stress biomarkers in pregnant women exposed to passive smoking [37]. The study reported a mean difference in 8-OHdG levels between treatment groups of approximately 12.96 ng/mL with a pooled SD of ~30.68 ng/mL, yielding a moderate effect size. Using a 1-sided test with *α*=.05 and 80% power, the minimum required sample size is 37 participants per group. To account for an anticipated 20% dropout rate, the sample size was increased to 44 participants per group, yielding a total of 88 participants.

Approximately 200 pregnant women attending routine antenatal care (ANC) visits at the community health centers were sequentially approached and invited to participate in the study. They were first interviewed to determine eligibility based on inclusion and exclusion criteria. Those meeting the criteria were provided with detailed information about the study and asked to provide written informed consent. Following consent, a blood sample was collected to assess baseline levels of heavy metals.

Only participants with elevated levels above reference thresholds were considered eligible for inclusion in the intervention phase. For the intervention group, eligible participants were contacted and provided with *M. oleifera* supplements along with instructions for daily consumption over a 2-month period. They were informed that a follow-up blood collection would occur at the end of the supplementation period during a routine visit.

For comparison, the control group was recruited from a different health center in a separate subdistrict administrative unit that did not receive moringa supplementation. This approach minimized contamination between groups and allowed for feasible implementation of the intervention. Follow-up blood sampling was also conducted after 2 months, aligned with their next scheduled antenatal visit, but without providing moringa supplementation.

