## Methods

### Study Design

This study is an ongoing quasi-experimental investigation that uses a nonrandomized pre-post test methodology. Expectant mothers were divided into 2 cohorts, one receiving an intervention and the other serving as a control. This study applied a nonrandomized pre-post test design due to practical considerations related to (1) practical management, (2) geographical differences, and (3) time constraints.

First, practical management considers that managing the study is easier when specific locations are designated for the intervention group and other locations for the control group. This approach ensures that the intervention (*M. oleifera* supplementation) can be efficiently delivered and monitored in each location without the complexity of randomizing participants across multiple sites. Furthermore, grouping participants by location helps streamline logistical operations such as monitoring compliance and ensuring consistent follow-up over the course of the intervention period.

Second, although the geographical settings of the intervention and control groups may differ, they were comparable in terms of demographic characteristics and environmental conditions. This allowed us to evaluate the effects of moringa supplementation in different geographical settings while maintaining comparability between groups. In addition, by focusing on distinct locations for intervention and control, we ensure better resource allocation and minimize the logistical challenges that would arise from attempting to randomize participants across a broader region.

Third, time was considered a constraint due to limitation in the laboratory. We could not receive heavy metal analysis results from the initial screening at the same time for all participants. Therefore, women with high levels of heavy metals at the first screening were included in the intervention group to avoid delays. This ensures that these participants can begin the 2-month intervention with *M. oleifera* as soon as possible after obtaining the result, considering the limited research timeframe. Furthermore, because we limited the overall time for the study, randomizing participants could cause delays in implementing the intervention and complicate the process of ensuring that those with high levels of heavy metals receive timely treatment.

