### Data Analysis

All analyses will be conducted using the R statistical software (latest version). Data entry and cleaning will be conducted by trained staff using a double-entry verification. For 24-hour food recall data, participants will be asked to estimate portion sizes using visual aids, and data will be reviewed during collection for completeness and clarity. For the FFQ, if participants leave implausible answers (eg, extremely high frequency), the data will be reviewed and clarified during the interview or excluded from analysis after documentation. Implausible intake frequency will be cross-checked with interview notes and food recall summaries to determine plausibility. An intention-to-treat (ITT) analysis will be performed to preserve the benefits of initial group allocation. For missing or partial responses, multiple imputation will be considered for covariates in the adjusted models. For missing outcome data at follow-up, last observation carried forward (LOCF) will be used when feasible. Sensitivity analyses will be conducted to assess the robustness of findings under different missing data assumptions. Outliers will not be automatically excluded unless clear reporting errors are confirmed. Outliers in biomarker measurement will be identified using the interquartile range method and retained unless proven to result from analytic error or sample contamination. All statistical analyses will be conducted with and without outliers to assess the robustness of the results.

Descriptive statistics will summarize participant characteristics. All continuous variables, including heavy metal concentrations and biomarker levels, will be checked for normality before analysis. In the case of non-normal distributions, appropriate data transformations (eg, log transformation) will be applied. If normality cannot be achieved, nonparametric tests (eg, Mann–Whitney *U* or Wilcoxon signed-rank test) will be used as alternatives. Analysis of group differences (pre- and postintervention). For each group, analysis will be conducted using the paired *t* test or Wilcoxon signed-rank test, depending on data distribution, to assess changes in heavy metals, MDA, and 8-OHdG levels before and after intervention. The significance level (alpha) will be set at .05, and all tests will be one-tailed.

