For comparison between the groups (intervention vs control), analysis will be conducted using the difference-in-differences (DiD) method to measure the difference in changes between the intervention and control groups. The results will provide an overview of the impact of moringa leaf supplementation on the reduction of heavy metal levels and prevention of DNA damage in pregnant women. To address potential selection bias and confounding due to the nonrandomized design, we will use analysis of covariance (ANCOVA) to adjust for baseline differences in key variables such as maternal age, gestational age, education level, and baseline levels of heavy metals, MDA, and 8-OHdG.

Assumptions for ANCOVA will be checked using diagnostic plots and tests. Normality of residuals will be checked using the Shapiro–Wilk test and Q-Q plots. The homogeneity of variance test will use the Levene test from the car package. Linearity and homoscedasticity will be checked using residual versus fitted plots.

The interaction effects between intervention status and baseline heavy metal levels will be examined by adding interaction terms to the ANCOVA models. Additionally, stratification will be considered a sensitivity analysis to minimize bias. Baseline heavy metal levels will be included as covariates in the statistical models to account for variation in environmental exposure across recruitment areas. In addition, we will conduct exploratory subgroup analyses to assess potential effect modifiers. Outcomes will be examined separately for each heavy metal to assess whether the reduction effect of *M. oleifera* differs by metal type. Additional exploratory subgroup analyses may include stratification by trimester of pregnancy, nutritional status (BMI), and geographic location/pollution source.

If substantial differences are observed, these findings will be interpreted cautiously due to limited statistical power. All subgroup analyses will be considered hypothesis generating and reported transparently. If no significant interaction is found, primary analyses will focus on aggregate outcomes across all participants. Reduction in each individual heavy metal will be reported separately, along with a composite index. No interim analyses or stopping rules are planned due to the short duration of the trial and the nature of the design.

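### Treatment is assigned by whole health centre (3 versus 3), but the between-group analysis and sample size ignore clustering, so the standard errors are too small if women of one centre are positively correlated

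*Protocol article*

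**What the plan says.** **Assignment.** Under Participant Recruitment, "Three centers were assigned as intervention sites and 3 as control sites based on operational convenience". Study Design gives the reason: "managing the study is easier when specific locations are designated for the intervention group and other locations for the control group". The six centres are "located in areas with varying environmental characteristics, including industrial zones, regions near landfill sites, and coastal areas". Under Intervention Group, capsule intake is supervised by health cadres attached to each centre.

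**Analysis.** Data Analysis names paired t or Wilcoxon tests within group, Mann–Whitney as a nonparametric fallback, difference-in-differences between groups, and ANCOVA on maternal age, gestational age, education and the baseline biomarkers. On sidedness: "The significance level (alpha) will be set at .05, and all tests will be one-tailed". The main models deal with area through one device: "Baseline heavy metal levels will be included as covariates in the statistical models to account for variation in environmental exposure across recruitment areas". Location or pollution source appears otherwise only as an optional exploratory subgroup.

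**Sample size.** "The study reported a mean difference in 8-OHdG levels between treatment groups of approximately 12.96 ng/mL with a pooled SD of ~30.68 ng/mL", taken as d = 0.42. With a one-sided test and "80% power, the minimum required sample size is 37 participants per group", raised to 44 for dropout. The same section also plans 59 per group, and Results reports 26 per group so far. No design effect is applied to any of these.

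**Who the controls are.** Later in Participant Recruitment, "the control group was recruited from a different health center in a separate subdistrict administrative unit", in the singular. Study Design adds that women found to have high levels at the first screening were placed in the intervention group so that they could start without delay.

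**The concern.** When whole centres carry the treatment, the comparison between arms is a comparison of three centres with three others. Women of one centre share air, water and food sources and, in the intervention arm, the same cadres. Whatever moves their biomarkers together over the 8 weeks appears in the difference between arms. An analysis that treats the women as independent counts that shared movement as if it averaged out over every woman, when it averages out only over centres.

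The sentence on baseline metals suggests that the matter is dealt with. It is not. Baseline adjustment or differencing removes stable centre differences in level. It leaves shared change during follow-up, and it leaves the correlation of the residuals.

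At stake are the interval and p-value for the primary outcome, the reduction in blood metals compared with control. All tests are one-tailed, so the relevant error is a false declaration of benefit. The Dissemination Plan foresees taking the results into city maternal health programmes.

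**Working it through.** **1. The plan's own figure.** d = 12.96/30.68 = 0.422, used as 0.42. With one-sided α = 0.05 and 80% power:

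- One-sample (paired) normal approximation: (1.645 + 0.842)²/0.42² = 6.18/0.1764 ≈ 35.1, so 36. With the t distribution it is **37**, the stated figure.
- Two independent groups: 2 × 6.18/0.1764 ≈ 70.1, so **71 per group**.

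So 37 reproduces as a within-group calculation. A two-group comparison needs 71 per group before any clustering. With independent women, two-group power would be 0.45 at 26 per arm, 0.63 at 44 and 0.74 at 59.

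**2. Effect of clustering.** Women per centre: m = n/3, that is 26/3 = 8.7, 44/3 = 14.7 and 59/3 = 19.7. The ICC is that of the baseline-adjusted change. The article does not give it, so 0.01, 0.05 and 0.10 are assumptions.

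- Design effect: DE = 1 + (m − 1) × ICC. The standard error is too small by √DE.
- True one-sided error of the unclustered test: 1 − Φ(1.645/√DE).
- Centre-level power: noncentral t on 6 − 2 = 4 df, critical value 2.13, noncentrality 0.42/√(2·DE/n).

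Example, 44 per arm and ICC 0.05: DE = 1 + 13.67 × 0.05 = 1.68; √DE = 1.30; 1.645/1.30 = 1.27, an error of 10.2%. Noncentrality = 0.42/√(2 × 1.683/44) = 1.52, a power of 0.35.

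| Per arm | ICC | DE | √DE | True error (formula) | True error (simulated) | Centre-level power |
|---|---|---|---|---|---|---|
| 26 | 0.01 | 1.08 | 1.04 | 5.6% | 5.8% | 0.33 |
| 26 | 0.05 | 1.38 | 1.18 | 8.1% | 8.4% | 0.28 |
| 26 | 0.10 | 1.77 | 1.33 | 10.8% | 11.4% | 0.24 |
| 44 | 0.01 | 1.14 | 1.07 | 6.1% | 6.2% | 0.46 |
| 44 | 0.05 | 1.68 | 1.30 | 10.2% | 10.4% | 0.35 |
| 44 | 0.10 | 2.37 | 1.54 | 14.2% | 15.0% | 0.28 |
| 59 | 0.01 | 1.19 | 1.09 | 6.6% | 6.5% | 0.53 |
| 59 | 0.05 | 1.93 | 1.39 | 11.8% | 11.9% | 0.39 |
| 59 | 0.10 | 2.87 | 1.69 | 16.6% | 17.2% | 0.30 |

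The simulation used 40,000 runs with no effect and 9, 15 or 20 women in each of 3 versus 3 centres. A t-test on the six centre means held between 4.9% and 5.2% at each of these settings.

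**3. The limit set by six centres.** With unlimited women in 3 versus 3 centres, the standard error cannot fall below √(2 × ICC/3). Power at d = 0.42 then cannot exceed about 0.60 at ICC 0.05 or 0.39 at ICC 0.10.

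**4. The passages on assignment.** One statement gives three control centres, another a single different centre, and Study Design sends women with high early screening results to the intervention. With three control centres the centre-level test has 4 df. With one, that arm has no between-centre variance estimate, and the df would be 3 + 1 − 2 = 2, on the assumption that the intervention arm's variance applies to both. If screening results also decided the arm, centre is not the whole assignment rule.

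**The case against.** - **The size is unknown.** This stands. Differencing and ANCOVA remove stable centre differences, so only the ICC of the adjusted change matters, and it may be small. At 0.01 the true error is 5.6% to 6.6%. The direction is certain for any positive ICC; the amount is not.
- **Independence is inferred from silence.** The article does not say how standard errors are computed, its covariate list is open-ended, and an unseen SAP could add clustering. This is only partly an answer. The article names the tests and covariates and states a remedy for area variation, and that remedy does not do what is claimed.
- **The limitation is already disclosed.** Strengths and Limitations concedes that environmental variability may confound, and the Discussion calls the findings hypothesis-generating. That covers bias. Correlated errors are not mentioned anywhere.
- **A reader might infer that a clustered analysis would stop centre differences being taken for a moringa effect.** It would not. Systematic differences between the two sets of centres are confounding, which no standard error removes.
- **A reader might infer that the pollution-source subgroup cannot be estimated because each centre has one treatment.** The article does not support this. The subgroup is by location or source, not by centre, and a source type may have centres in both arms. What would be lacking, with so few centres per type, is a valid error term.
- **The singular control centre may be loose wording.** It may be; three is stated explicitly elsewhere. It needs clarifying because the degrees of freedom depend on it.

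**Conclusion.** The concern holds as a matter of variance. The stated between-group analysis does not respect assignment by centre, and the claim that baseline metals account for variation across recruitment areas is wrong. For an assumed ICC of 0.01 to 0.10, the nominal 5% one-sided error is really about 5.5–11% at 26 per arm, 6–15% at 44 and 7–17% at 59. These figures rest on three equal-sized centres per arm and on an ICC that the article does not supply; confidence in the direction is high, in the size moderate.

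It should not be read as showing that the estimate is biased by a known amount, that the subgroup is inestimable, or that there was in fact only one control centre. The 80% power is not supported for the between-group comparison, with or without clustering.

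**What to change.** 1. Base the primary between-group interval and test on centre: either baseline-adjusted centre means, on 4 df if there are three centres per arm, or a random-centre model with small-sample degrees of freedom. The centre-mean test was checked by simulation here; the mixed model with six centres was not.
2. Show results for each centre, and label the individual-level result as not accounting for clustering.
3. Correct the Data Analysis sentence: baseline metals adjust for prior level only.
4. Reconcile the three accounts of assignment (three control centres, one different centre, early high screening results to intervention) and state the number of control centres. If there was one, say that between-centre variance cannot be estimated in that arm.
5. State that the centre-based analysis corrects the error bars and not confounding from non-random assignment.
6. Report the pollution-source subgroup descriptively only.
7. Withdraw the 80% power claim for the between-group comparison.

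**Cost.** Analysis wording, with no new data; laboratory work was still under way in February 2025. The one-sided critical value rises from about 1.68 (50 df at 26 per arm) to 2.13 (4 df), and intervals widen. Centre-level power at d = 0.42 is about 0.24–0.33 at 26 per arm (0.25–0.34 if centre size is rounded up to 9) and 0.28–0.46 at 44. That loss reflects how little information 3 versus 3 centres carry.

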**Results:**

A total of 26 mothers for each group have participated. As of February 2025, the laboratory analyses have been ongoing, and the result is expected to be published at the end of 2025. The protocol anticipates that the intervention group will show a significant reduction in both heavy metal levels and oxidative stress biomarkers compared to the control group, suggesting the potential efficacy of *M. oleifera* in detoxifying heavy metals and reducing oxidative stress.

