## Results

Overview

The study was funded in 2024 and data collection began in July 2024. A total of 26 mothers in each group have participated. As of February 2025, the laboratory analysis is ongoing for the second step. We expect the results to be published at the end of 2025.

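### Two planned sizes (59 and 44 per group) stand unreconciled, the 20% dropout inflation is wrong, and the base figure of 37 fits a paired test, not the between-group comparison

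*Protocol article*

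**What the plan says.** Under Participant Recruitment the target appears first as "The study will include 59 pregnant women in each group of intervention and control", which is 118 women. The sample-size paragraph of the same section then gives a different target. It starts from an effect size of 0.42, obtained from a "mean difference in 8-OHdG levels between treatment groups of approximately 12.96 ng/mL with a pooled SD of ~30.68 ng/mL". It continues: "Using a 1-sided test with *α*=.05 and 80% power, the minimum required sample size is 37 participants per group". It ends: "To account for an anticipated 20% dropout rate, the sample size was increased to 44 participants per group, yielding a total of 88 participants".

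The Results section reports "A total of 26 mothers in each group have participated", and the Abstract says the same. Study Design describes the study as ongoing. By February 2025 laboratory analysis was in its second step.

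Data Analysis plans a paired t test or Wilcoxon signed-rank test within each group. Between groups it plans difference-in-differences (DiD), with ANCOVA adjusting for baseline biomarkers among other variables. All tests are one-tailed at .05.

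**The concern.** A protocol should have one planned size, traceable to a calculation for a named comparison. Here two targets differ by 15 women per group, and the derived one uses an inflation that does not protect the minimum it starts from. The derivation also appears to pair a between-group effect size with a formula for a within-group test. The only participation count given is below both targets and below the uninflated 37.

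A reader therefore cannot tell what the trial was sized for, or whether it fell short. A null between-group result could be read as coming from a study with 80% power when the document does not support that.

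**Working it through.** **Inputs** (Participant Recruitment unless noted): mean difference 12.96 ng/mL, pooled SD 30.68 ng/mL, d = 0.42, one-sided α = .05, power 80%, 20% dropout. Stated sizes are 37, 44 and 59 per group; 26 per group is reported in Results. The baseline-to-follow-up correlation r is not given, so it is varied below.

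**1. Effect size.** 12.96/30.68 = 0.422. The stated 0.42 is consistent.

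**2. Base size of 37.**
- Paired (one-sample) test: n = ((1.645 + 0.842)/0.42)² = 35.05, so 36. The exact noncentral-t calculation gives **37** (power 80.5%), which is the stated figure.
- Two-sample test: n = 2 × ((1.645 + 0.842)/0.42)² = 70.1, so **71** per group. The exact t calculation also gives 71. At 37 per group this test has 56% power.

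So 37 is the paired figure, although d was taken from a difference between groups.

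**3. Could baseline adjustment rescue 37?** ANCOVA multiplies the required n by (1 − r²). Setting 70.1 × (1 − r²) = 37 gives 1 − r² = 0.528, so r ≈ 0.69. The protocol states no correlation.

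**4. Dropout.**
- 37 × 1.2 = 44.4, which gives the stated 44.
- To retain 37 after 20% loss: 37/(1 − 0.20) = 46.25, so 47.
- 44 × 0.8 = 35.2, so about 35 completers. Paired power at 35 is 78.5%.
- Applied to the unadjusted two-sample size: 71/0.8 = 88.75, so 89 per group.

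**5. The target of 59.** No derivation is given. At 59 per group with no loss, the unadjusted two-sample test has 73% power, so this target does not reach 80% for that test either.

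**6. Power at 26 per group** (d = 0.42, one-sided .05, no allowance for clustering by health center). The paired within-group test has 67%. For the between-group test, d is divided by √(1 − r²) for ANCOVA and by √(2(1 − r)) for DiD on change scores:

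| r | ANCOVA power | ANCOVA detectable difference (80% power) | DiD power |
|---|---|---|---|
| 0 | 44% | 0.70 SD | 28% |
| 0.5 | 53% | 0.61 SD | 44% |
| 0.7 | 67% | 0.50 SD | 61% |
| 0.8 | 80% | 0.42 SD | 76% |

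The detectable difference is 0.70 × √(1 − r²). For DiD it runs from 0.99 SD at r = 0 to 0.44 SD at r = 0.8.

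**The case against.** **The 26 is not a planned size.** A reader might infer a third target, or that recruitment stopped short. The text supports neither: 26 is a count of participants in a study described as ongoing, and the 80% claim is attached to 37. What stands is that the document does not say whether 26 is final, or whether it counts women enrolled or women with follow-up samples. For the latter reason, taking a further 20% off the 26 would not be justified.

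**No single between-group power can be quoted.** A reader might take 44%, the unadjusted two-sample figure, as the power at 26 per group. The planned analyses use baseline values, so their power depends on r, and with ANCOVA at r = 0.8 even 26 per group reaches 80%. This objection holds, which is why a range is given. It does not rescue the 80% claim, because the protocol assumes no correlation.

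**The inflation slip is minor.** On the paired basis it costs less than two percentage points. That is right; it is an arithmetic error to correct, not the main loss of power.

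**The origin of 59 is unknown.** A reader could construct a calculation that yields 59, but none is documented, so no contradiction with the one-sided test can be claimed. The conflict with 44 does not depend on where 59 came from.

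**Limited power is already admitted.** Strengths and Limitations says in general terms that sample size may limit power. It gives no figure, mentions no shortfall and does not withdraw the 80%.

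**Conclusion.** The point holds in this form. Two planned sizes, 59 and 44 per group (118 and 88 in total), cannot both be right. The inflated figure should be 47 if 37 is kept as the base, but 37 is itself only the size for a one-sided paired test. For the between-group comparison that the effect size describes, an unadjusted test needs 71 per group (89 after 20% loss). The 80% claim carries over to ANCOVA at 37 completers per group only under an unstated correlation of about 0.7.

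These figures assume d = 0.42, one-sided .05, equal groups and no clustering by health center. It remains open whether the trial is underpowered at its final size, because the status of the 26 and the correlation are not given.

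**What to change.** - State one planned size throughout, with its derivation and the comparison it is for. If that is the between-group comparison, use a two-group formula and state any assumed baseline-to-follow-up correlation with its source.
- Inflate by n/(1 − 0.20). Changing 44 to 47 alone is not enough, because it keeps the paired base figure.
- State whether 26 per group is final, and whether it counts enrolled women or completers.
- If 26 is final, keep the original target on record and report the shortfall against it. Replace the 80% claim with achieved one-sided power: 67% for the paired within-group test and, for the between-group ANCOVA, the range over r (44% at 0, 53% at 0.5, 67% at 0.7, 80% at 0.8), with a detectable difference from 0.70 down to 0.42 SD. If DiD on change scores is the lead analysis, give its range instead.

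The cost is a text correction and a less favourable stated power. It requires no added participants, but if the size is re-derived for the between-group comparison the stated target will probably rise.
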